**Fig. 3 Fig3:**
[figure not shown]
Simulations of the interim analysis. **A** The number of correct interim decisions—where an interim was stopped where there was no significant finding or continued for effect sizes of 0 and 0.6. Error bars indicate 95% confidence intervals generated by bootstrapping the simulation results sampling 100 results 1000 times. **B** The change in mean % correct interim decisions as more subjects are added to interim. The interim number 15 was chosen as the relative benefit of adding more decreases above this point. **C** The effect of number of subjects on overall interim pass rate. This figure displays the % of interims that would go on to recruit a full study from populations of fixed effect sizes

If the interim analysis predicts >  = 80% statistical power using an estimated effect size then a hypothesis test will be performed using O’Brien-Fleming alpha-spending criteria:If the null hypothesis cannot be rejected at this point then recruitment of this minor allele group along with the control group will continue to the end of the planned cohort.Else if the null hypothesis can be rejected then this minor allele group will stop. The study will continue with recruitment of the next planned minor allele group.If the interim analysis predicts < 80% statistical power then recruitment of this minor allele group will stop and individuals from next minor allele group will be recruited. Recruitment will again be continued up to the pre-specified interim analysis (repeat analysis step (1))

This process will be repeated iteratively until the full cohort has been assessed (N = 100) as directed by the recruitment plan (see Fig. 2).

The interim and final analyses will use data from the Control group as the comparator therefore, to maintain equally sized groups at the end of the study and to maintain study group masking, the rate of recruitment into the Control group will reduce after each adaptation in minor allele group recruitment. The changes in recruitment strategy will be directed by the interim analysis committee and implemented by an independent group within the ALSPAC participant recruitment team.

In the event of all minor alleles being underpowered for differences in heat pain threshold, as determined by the interim assessments, additional endpoints derived from the secondary measures (QST and flare) will inform the final group recruitment (see Fig. 3 and Table 2 which illustrate the adaptive design and its effects upon recruitment).

**Table 2 Tab2:** Interim analyses

Interim analysis #	Futility effect size	Efficacy cut-off alpha	Effect size req. for statistical eff (ΔHPT)
1	0.57	0.0013	1.63 (Δ4.1 °C)
2	0.62	0.0023	1.52 (Δ3.8 °C)
3	0.68	0.0055	1.42 (Δ3.5 °C)

Each row indicates the study state at subsequent interims. Effect sizes are displayed as Cohen’s d $$\frac{{\left( {\mu_{minor} - \mu_{major} } \right)}}{\sigma }$$ where µ is the mean and σ is the standard deviation. The futility effect size cut-off is the minimum effect size required to continue the group in the study. The futility effect size is calculated as the smallest effect size observable at the final analysis at 80% probability given an alpha cut-off of 0.05. The efficacy cut-off alpha is the alpha criteria for the interim analysis to determine efficacy. The efficacy cut-off alpha is calculated using an O’Brien-Fleming alpha spending through the gsdesign R package. With subsequent interims the alpha threshold is relaxed as the proportion of information known at interim increases due to the fixed sample size of 15. The effect size required for statistical efficacy (HPT) indicates the minimum effect size (cohen’s d) likely to be observed at 80% power at interim with the corresponding changes in HPT (Δ) indicated assuming σ = 2.5. HPT, heat pain threshold

We will follow the applicable Food and Drug Administration (FDA) guidelines for adaptive trial design [43]. To maintain the integrity of the sampling frame through this experiment, the analysis script is stated a priori and researchers involved in the data collection will not be aware of the outcomes of any interim analysis nor changes in the recruitment strategy; and therefore remain blind to genotype throughout.

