### Interim assessment strategy

Interim assessments will be used to determine if the recruitment of the minor allele group should be changed given the likelihood of observing a detectable effect (80% power, ⍺ ≤ 0.05 using independent two tailed t-test) at the end of the study (see Fig. 2). To reduce the impact of performing interim assessments, the criteria for adapting the study are stated a priori and an O’Brien-Fleming alpha spending is used after each hypothesis test [42].

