### Data analysis

The hypothesis test at interim and final analysis will be performed using a two-sided independent t-test. The type-1 error is controlled using the O'Brien-Fleming alpha spending method for the primary outcome measure, the heat pain threshold. Other QST variables will only be analysed at the final analysis. All other comparisons between available groups will be treated as exploratory. The genotype of the individuals will also be considered to qualify the association of SNP to any observed effect.

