### Efficacy

The estimated effect size is commonly used to determine the number of participants to recruit for a study, however if the estimated mean effect size is lower than the actual mean effect within the sampled population then more participants will be recruited than is required to observe the effect. If we consider where we observe a large 4 °C change in heat pain threshold, a recall by genotype would have an 80% chance of observing this effect after the first seven participants per group (given our expected standard deviation 2.5 °C), however the full cohort would still have been recruited. In our study, there is a 77.6% chance of observing a 4 °C change at the first interim with fifteen participants per study arm resulting in less assessment of individuals with a hypersensitivity to noxious stimuli.

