### Statistical considerations

Unblinded assessment of effect size at interim has the potential to impact the final statistical analysis. For example, if an interim analysis performs a hypothesis test to reject the null hypothesis then it introduces a testing multiplicity which will increase the likelihood of type 1 errors (false positives) in the final analysis. A common approach to take account of the interim assessment is to split the alpha criteria across the additional interims, referred to as alpha spending. In its simplest form the critical value threshold is divided equally amongst the interims including the final analysis [46]. For example, the addition of an interim analysis with a desired final alpha of 0.05 results in an adjusted alpha threshold of 0.025 at the interim and final analysis stage giving an equal weight to both analyses. More commonly, alpha spending strategies which consider the available information at the time of interim assessment are employed such as the O’Brien–Fleming method, which divides the alpha threshold by the number recruited at interim relative to the total number of participants [42]. In the case where a single interim is performed after half of the participants are recruited the effect is the same as the Pocock adjustment. However, where the interim occurs with less than half, a larger effect size is required to stop for efficacy than at the end of the study which accounts for the lower confidence associated with the fewer participants earlier in the study. We opted for the O’Brien-Fleming approach as we desired to perform interim at an early timepoint to allow screening of more alleles; we expect small effect sizes and therefore will only stop for efficacy at interim where the effect is very robust; and desire the interim to have minimal impact on the final analysis.

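### Table 2's efficacy cut-offs do not match the stated two-sided 0.05 O'Brien-Fleming design, row 2 contradicts itself, and the 77.6% early-detection figure rests on a cut-off that is too lenient

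*Protocol article*

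**What the plan says.** The Data analysis section fixes the sidedness: "The hypothesis test at interim and final analysis will be performed using a two-sided independent t-test". The Interim assessment strategy section agrees, setting 80% power and alpha of at most 0.05 "using independent two tailed t-test".

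Table 2 gives the cut-offs 0.0013, 0.0023 and 0.0055 for interims 1 to 3. Its note says "The efficacy cut-off alpha is the alpha criteria for the interim analysis to determine efficacy", and adds: "The efficacy cut-off alpha is calculated using an O’Brien-Fleming alpha spending through the gsdesign R package". Beside each cut-off stands an effect size, 1.63, 1.52 and 1.42 (4.1, 3.8 and 3.5 °C at SD 2.5 °C), which "indicates the minimum effect size (cohen’s d) likely to be observed at 80% power at interim".

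The Discussion, under Efficacy, says "In our study, there is a 77.6% chance of observing a" 4 °C difference at the first interim, with 15 per arm. Under Statistical considerations, it says that the O'Brien-Fleming method "divides the alpha threshold by the number recruited at interim relative to the total number of participants", and that with one interim at half of recruitment "the effect is the same as the Pocock adjustment".

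**The concern.** These cut-offs are the pre-specified rule for stopping an allele group for efficacy. If they come from a one-sided 0.05 boundary but are applied to two-sided p-values, early stopping is easier than the stated design allows, and the article's detectable effects and early-detection probability are too favourable. A two-sided p of 0.001 at the first interim, for example, stops the group under Table 2 but not under a two-sided O'Brien-Fleming bound.

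Row 2 raises a second problem. Its cut-off and its effect size do not belong together, so a reader cannot tell which was calculated. The explanation of the method in the Discussion also fits neither Table 2 nor O'Brien-Fleming.

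**Working it through.** **Inputs.** Interim at 15 per group; total N = 100; SD 2.5 °C; two-sided 0.05 tests. The final group sizes are inferred, because Fig. 2 is not shown. Each abandoned allele group uses 15 people, so the final size per group is 100/2 = 50, then (100 − 15)/2 = 42.5, then (100 − 30)/2 = 35. The futility column supports this: a two-sided 0.05 t-test with 80% power detects d = 0.566, 0.619 and 0.679 with 50, 42 and 35 per group, against the printed 0.57, 0.62 and 0.68. The information fractions t are then 15/50, 15/42 and 15/35.

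**Boundary.** With one interim at t, the classical bounds are C/√t at interim and C at the end; the two statistics have correlation √t.
- One-sided 0.05: solve P(Z1 ≥ C/√t or Z2 ≥ C) = 0.05.
- Two-sided 0.05: solve P(|Z1| ≥ C/√t or |Z2| ≥ C) = 0.05.

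| Row | t | Printed | One-sided 0.05 design, one-sided p | Two-sided 0.05 design, two-sided p (15 v 15) |
|---|---|---|---|---|
| 1 | 15/50 | 0.0013 | 0.00129 | 0.00034 |
| 2 | 15/42 | 0.0023 | 0.00279 | 0.0010 |
| 3 | 15/35 | 0.0055 | 0.00546 | 0.0026 |

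Rows 1 and 3 match the one-sided design to every printed digit.

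**Effect-size column.** This uses the noncentral t with 28 degrees of freedom and noncentrality d√(15/2), solved for 80% power.
- Two-sided at 0.0013: d = 1.633. Two-sided at 0.0055: d = 1.420. Both are as printed.
- One-sided use of the same cut-offs would give 1.53 and 1.31.

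So the table takes one-sided bounds and then uses them as two-sided levels.

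**The 77.6%.** For 4 °C, d = 4/2.5 = 1.6. A two-sided test at 0.0013 with 15 per group has power 0.7761, which reproduces the article's figure. Row 1 under the stated two-sided design gives:
- Classical bound, C = 1.9612: interim z = 1.9612/√0.30 = 3.581, p = 0.00034. Power for 4 °C is 62%, and 80% power needs d of about 1.83, or 1.83 × 2.5 = 4.6 °C.
- Lan-DeMets O'Brien-Fleming-type spending: p = 4[1 − Φ(2.2414/√0.30)] = 0.000085. Power for 4 °C is about 44%.

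**Row 2.** Two-sided at 0.0023 gives d = 1.55 (1.55 × 2.5 = 3.9 °C), not 1.52 (3.8 °C). A cut-off of 0.0028 gives 1.521, and 0.0028 is also the table's own one-sided value at 15/42. To obtain 0.0023 by that route needs about 44 per group, for which the futility d would be 0.604, not 0.62.

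**Description in the Discussion.** Scaling 0.05 by the recruited fraction gives 0.05 × 0.30 = 0.015 at the first interim and 0.05 × 0.5 = 0.025 at half. The second figure is the equal split that the article calls Pocock. O'Brien-Fleming at half information is 0.0052.

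**Type 1 error for one allele comparison**, with the printed cut-offs read as two-sided:
- Final test at 0.05, futility ignored: 5.07%, 5.11% and 5.26%.
- Final test at the matching bound read the same way (0.0494, 0.0488, 0.0478), futility ignored: about 5.0% to 5.05%.
- Final test at 0.05 with futility stopping on the absolute effect size, simulated with equal groups: about 2% in each row.

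**The case against.** A reader might infer from the last column of the table that all three cut-offs are two to four times too lenient (0.0013/0.00034 = 3.8, 0.0023/0.0010 = 2.3, 0.0055/0.0026 = 2.1). That is secure only for row 1. The Interim assessment strategy section says control recruitment slows after each adaptation but does not stop, so interims 2 and 3 may compare 15 minor-allele participants with more than 15 controls. Using the harmonic mean, 2 × 15 × m/(15 + m), as the effective size per group, the two-sided bound at interim 2 is 0.0023 with m = 21 and 0.0032 with m = 25. At interim 3 it is 0.0056 with m = 22 and 0.0082 with m = 29. If controls are paced evenly towards equal final groups, m is about 15 + 15 × 27.5/42.5 = 25 at interim 2 and about 25 + 15 × 10/35 = 29 at interim 3. The printed rows 2 and 3 would then be stricter than required. Nothing shows that the article used this route, and its effect-size column assumes 15 v 15, but the possibility rules out 0.0010 and 0.0026 as settled replacements.

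A reader might also infer that the type 1 error is not held. The documents do not support that. The excess is 0.07 to 0.26 percentage points, and only if the final test stays at 0.05 and futility stopping is ignored. With the matching final bound it nearly vanishes, and with futility stopping the error falls well below 5%.

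Two further points stand. The 77.6% is not a separate slip; it is exact at the printed 0.0013 and changes only if row 1 changes. And the faulty description of O'Brien-Fleming is Discussion prose, not the operating rule, which is Table 2.

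**Conclusion.** The point holds in this form. Rows 1 and 3 of Table 2 are one-sided values from a one-sided 0.05 design, used as two-sided levels although the article specifies two-sided 0.05 tests. Row 1 is about four times too lenient against the classical bound, and the chance of detecting 4 °C at the first interim is overstated by about 16 points (77.6% against 62%), or by more under the spending-function reading. Row 2 is inconsistent on any view of sidedness. The Discussion's equation of O'Brien-Fleming with Pocock at half information is wrong.

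This rests on the inferred fractions, which the futility column supports, and on 15 v 15 at the first interim. The size of any error in rows 2 and 3 against the two-sided design is not established. The type 1 error figures concern one allele comparison, not the three together.

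**What to change.** Rerun gsDesign as a two-sided design (test.type=2, alpha=0.025). State whether the classical bound or the spending function is used, and give the information fraction at each interim from the actual minor-allele and control numbers. Then:

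- replace the row 1 cut-off with about 0.0003 (classical), or about 0.000085 if the spending function is chosen;
- recompute rows 2 and 3 from the stated fractions; 0.0010 and 0.0026 apply only to the classical bound with exactly 15 v 15;
- state the matching final alpha for each path (classical and 15 v 15: about 0.0499, 0.0496 and 0.0489);
- update the effect-size column, and change the 77.6% to about 62% (classical) or about 44% (spending function);
- rewrite the Discussion's account of O'Brien-Fleming and remove the claim that it equals Pocock at half information.

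If a one-sided 0.05 design was intended, keep the one-sided cut-offs of rows 1 and 3, correct row 2, and change the two-sided statements under Interim assessment strategy and Data analysis, the effect-size column and the 77.6% instead (power for 4 °C with a one-sided test at 0.0013 is 84.4%).

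The cost is one software run and edits to one table and a few sentences. Under the two-sided design, early efficacy stopping at the first interim becomes rarer; the total sample does not change.

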**Fig. 2 Fig2:**
[figure not shown]
Schematic of study design showing the 4 potential outcomes of the adaptive design. The trial progresses from left to right until the full sample of 100 is recruited. Each allele cohort is noted with uniquely coloured human icon with the numbers recruited in that phase noted underneath. Interim assesments are marked with a magnifying glass with the effect size ‘d’ criteria to continue the trial noted and alpha thresholds for subsequent t-test. Note that the trial will adapt due to small effect sizes and also if the hypothesis test passess due efficacy. The final “?” represents that this final cohort could be from any of the final cohorts based on assesment of other outcomes. For further details on the outcome criteria see Table 2

Individuals homozygous for the minor allele(s) and individuals from the control allele group will be recruited until at least 15 members have been recruited to both groups (as determined by simulations see Fig. 3). At this point, an interim analysis will be performed:

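### Table 2 sets the efficacy thresholds at interims 2 and 3 for 15 v 15, but the recruitment rule implies more than 15 controls by then, so those rows are stricter than intended and overstate the effects needed

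*Protocol article*

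**What the plan says.** All of this is in the protocol article, under the heading on interim assessment strategy.

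- **Trigger.** The first minor-allele group and the controls are "recruited until at least 15 members have been recruited to both groups". The process then repeats with the next group, up to 100 participants in all.
- **Comparator.** "The interim and final analyses will use data from the Control group as the comparator". The aim is "to maintain equally sized groups at the end of the study" and to preserve masking. To that end, "the rate of recruitment into the Control group will reduce after each adaptation in minor allele group recruitment".
- **Table 2.** The efficacy alphas are 0.0013, 0.0023 and 0.0055. The effects required for efficacy at 80% power are d = 1.63, 1.52 and 1.42 (4.1, 3.8 and 3.5 °C at SD 2.5 °C). The futility effects are 0.57, 0.62 and 0.68. The note explains the rising alphas thus: "With subsequent interims the alpha threshold is relaxed as the proportion of information known at interim increases due to the fixed sample size of 15".

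**The concern.** The information in a two-group comparison depends on both group sizes. Table 2 counts 15 people per group at every interim. The recruitment rule describes a single Control group that has at least 15 members at interim 1 and goes on growing, more slowly, while groups 2 and 3 are recruited. If so, interims 2 and 3 compare 15 minor homozygotes with more than 15 controls and carry more information than the table assumes.

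The efficacy alpha is a decision threshold: it settles whether an allele group stops early and the next one starts. If it is set for too small an information fraction, it is stricter than the O'Brien-Fleming boundary the authors chose, and the table understates what those two interims can detect.

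**Working it through.** **Inputs.** From the protocol article: N = 100; interim at 15 per group; equal groups at the end; two-sided t-test; O'Brien-Fleming boundary; 80% power; SD 2.5 °C; the Table 2 figures. Assumed: controls accrue at a constant reduced rate that ends in equal groups.

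**Formulas.**
- Power: noncentral t with n1 + n2 − 2 degrees of freedom and noncentrality d·√[n1·n2/(n1+n2)].
- Boundary: two looks, critical values C/√t and C, with correlation √t between the looks. C is chosen to give the overall error, and the nominal interim alpha (one-sided) is 1 − Φ(C/√t).
- Information fraction: t = [n_minor·n_control/(n_minor+n_control)] ÷ (final n per group/2).

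**Step 1: final group sizes.** If group 1 stops at 15, then 100 − 15 = 85 remain for the final comparison, or 42.5 per group. If group 2 also stops at 15, 70 remain, or 35 per group. The 80%-power effects at 50, 42 and 35 per group (two-sided 0.05) are 0.566, 0.619 and 0.679. These are the futility figures, so that column counts the earlier controls.

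**Step 2: the efficacy columns as 15 v 15.**
- Row 1: t = 15/50 with a one-sided 0.05 boundary gives alpha 0.00129. At 0.0013, 15 v 15 needs d = 1.633. Both match.
- Row 3: t = 15/35 gives alpha 0.00546. At 0.0055, 15 v 15 needs d = 1.420. Both match.
- Row 2: t = 15/42.5 gives alpha 0.0027 (0.0025 to 0.0028 for 15/43 to 15/42), not 0.0023. At 0.0023, 15 v 15 needs d = 1.55; the printed 1.52 corresponds to alpha 0.0028. The row does not agree with itself, but it is far from a 25-control comparison, which needs about 1.36 at 0.0023.

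**Step 3: controls under even accrual.**
- Interim 2: 15 + 27.5 × 15/42.5 = 24.7.
- Interim 3: 24.7 + (35 − 24.7) × 15/35 = 29.1.

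**Step 4: information fractions.**
- Interim 2: (15 × 24.7/39.7)/21.25 = 9.33/21.25 = 0.44, against 15/42.5 = 0.35.
- Interim 3: (15 × 29.1/44.1)/17.5 = 9.90/17.5 = 0.57, against 15/35 = 0.43.

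**Step 5: consequences.**

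| | Interim 2 (15 v 24.7) | Interim 3 (15 v 29.1) |
|---|---|---|
| Printed alpha; printed d | 0.0023; 1.52 | 0.0055; 1.42 |
| Power at printed d and printed alpha | 90% | 93% |
| d for 80% power at printed alpha | 1.36 (3.4 °C) | 1.21 (3.0 °C) |
| One-sided 0.05 boundary: alpha; d | 0.0059; 1.24 (3.1 °C) | 0.012; 1.10 (2.8 °C) |
| Two-sided 0.05 boundary: alpha; d | 0.0029; 1.33 (3.3 °C) | 0.0083; 1.155 (2.9 °C) |

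The one-sided boundary is shown because it reproduces rows 1 and 3; the two-sided one because the test is two-sided. Which of them should apply is a separate question. The printed alphas are too strict on either basis.

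**Step 6: range if accrual is uneven (one-sided basis).**
- Interim 2, 16 to 42 controls: t 0.36 to 0.52, alpha 0.0030 to 0.0099, d 1.48 to 1.06.
- Interim 3, 16 to 35 controls: t 0.44 to 0.60, alpha 0.0061 to 0.0143, d 1.38 to 1.05.

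Any count above 15 moves the figures in the same direction.

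**Step 7: type I error.** With the printed interim alphas, the final critical value that goes with the 15-per-group fraction, and the larger fractions of step 4, the one-sided error of each two-look comparison is 0.0496 and 0.0492, just under 0.05.

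**The case against.** The best defence is that 15 v 15 can be squared with the final group sizes. If controls paused after interim 1, interim 2 would fall at 45 participants, and the other 55 could be recruited 1:1 (27.5 each) to reach 42.5 per group. The arithmetic works, but the text speaks against it twice. A rate already at zero cannot fall again at the next adaptation, and testing only minor homozygotes between interims would undo the masking that the rule is meant to protect.

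Several other objections stand in whole or part:
- The counts of 25 and 29 are not in the visible text, and Fig. 2, which its legend says shows the numbers per phase, is not available here. Use of every accumulated control at an interim is inferred from the comparator sentence and the final group sizes. A reader should not take 25 and 29 as stated by the rule.
- A reader might infer that Table 2 is faulty because its futility and efficacy columns use different sample sizes. That alone is no fault: one column describes the final analysis and the other the interim.
- A reader might also infer that the interim committee cannot know which controls to use. The article says the analysis script is fixed in advance; it is not shown and may already use the actual counts.
- Under the heading on statistical considerations, the authors want early efficacy stops only for very robust effects, so a strict threshold suits their aim. A group that misses it also continues to the final test. At the minimum relevant effect, d = 0.6, the chance of crossing the printed alpha moves only from about 6% to 9% (interim 2) and from 11% to 17% (interim 3).

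These points limit the consequence. They do not make rows 2 and 3 describe the comparison that the recruitment rule sets up.

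**Conclusion.** The point holds, at moderate weight. Table 2's efficacy columns are built on 15 v 15, whereas the stated recruitment rule and the article's own final effects imply more than 15 controls at interims 2 and 3. The direction is firm; the size depends on control accrual. Under even accrual the printed alphas of 0.0023 and 0.0055 are stricter than the intended boundary, though only slightly so at interim 2 on a two-sided basis (0.0029). For a true 3 °C effect (d = 1.2), the chance of crossing the printed alpha is about 65% rather than 49% at interim 2, and 80% rather than 61% at interim 3.

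It would be wrong to read this as an inflated false-positive rate. By this route the error is conservative, and the futility cut-offs stand. What is wrong is a decision threshold tighter than the method named, and required effects that are too large.

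**What to change.** 1. State that each interim compares the current minor-allele group with all controls tested to date.
2. Have the pre-specified script compute the information fraction as [n_minor·n_control/(n_minor+n_control)] divided by its planned final value. Use actual counts, since the trigger is a minimum of 15 and either group may exceed it.
3. Re-derive alpha and required effect together for rows 2 and 3, from the planned control counts (those in Fig. 2, if it gives them). Under even accrual the pairs are about 0.0059 with 1.24 and 0.012 with 1.10 on the one-sided 0.05 boundary, or 0.0029 with 1.33 and 0.0083 with 1.155 on a two-sided one. Do not pair new alphas with 1.36 and 1.21, which hold only at the printed alphas.
4. Check row 2 in its own right: at 15 v 15, alpha 0.0023 goes with d = 1.55, not 1.52.
5. Replace the part of the Table 2 note that attributes the rising alphas to 15 per group.

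If 15 v 15 is what is meant, say instead which 15 controls are used and reconcile that with the recruitment rule. Either way the cost is two recalculated rows, one sentence and a small script change, with no extra participants or procedures.
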